### Procedures: study phase 2 (Specific Aims 2 and 3) — months 23–42

Phase 2 uses a survey of parents of ASUDs (n = 400) to serve two goals: 1) establish the psychometric properties of the PSQ, and 2) elucidate the marketing preferences of ASUD parents using the Marketing Mix framework. Surveys are often used in marketing research to test initial qualitative findings using direct questions in larger, more representative samples [26].

### Survey construction

In addition to containing the measures used in Phase 1, the survey will contain the PSQ and a series of questions about service preferences (about 40 items). Items about service preferences will be developed based on feedback from Phase 1 and will cover each element of the Marketing Mix framework. An example of a question from the “Place” component might be a multiple-choice item indicating where parents prefer to receive their information about ASUD treatment, with response options based on the data from Phase 1. Also, parents will be asked to rank-order their preferred targeted marketing messages from Phase 1.

### Sampling considerations

Several sampling frames were considered for the survey, each of which had benefits and tradeoffs. First, a nonprobabilistic (or nonrandom) online survey was considered, as this approach is commonly used in marketing research [70]. As noted in Zeithaml et al.’s best-selling services marketing textbook [26], the benefits of online surveys include: broader geographic representation; enhanced accuracy and completeness of answers; speed; reduced costs; and streamlined data analysis. However, this approach was ruled out due to concerns about selection bias and limited coverage of individuals without internet access [71]. Second, community-based recruitment was contemplated, as this approach is common in treatment research. Although this approach yields a nonprobabilistic sample, it protects against some of the concerns about the reach of an online sample by facilitating proactive recruitment of low-income and under-represented populations. Finally, various methods to recruit a probabilistic sample were considered, each of which would require members of the target population to have an equal and random chance of selection [72]. This approach would involve random selection of participants from a known sample of parents of ASUDs through national registries, school rosters, or other means. Although this approach would yield the largest benefits in terms of representativeness, its execution would require the largest investment of time and financial resources. As such, probabilistic sampling was deemed beyond the scope of this protocol, which was funded by a Research Career Development Award (K23) and designed to collect preliminary data sufficient to establish proof of concept.

Based on the aforementioned considerations, the survey will use multimethod, single-mode sampling, combining community-based and online recruitment. Within each method, quota sampling will be used to promote representativeness with regard to geography, race/ethnicity, gender, and parent characteristics in order to more closely approximate a probabilistic sample [72]. All participants will be administered the survey using a web-based browser to prevent confounds associated with modality. The community sample will complete the survey on a laptop during an in-person study session, while the online sample will complete the survey from a computer of their choosing. The online sample will be restricted to the six-state New England area in order to promote consistency with the community sample. Reflecting the differential level of effort required, participants in the community will receive $50, while those in the online sample will receive $25.

### Online recruitment

One-quarter to one-half of the survey participants will be recruited through the clinics used in Phase 1. Remaining participants will be recruited online, using an existing website of the American Psychological Association’s (APA) Division 53 (Society of Clinical Child and Adolescent Psychology). The website (http://www.effectivechildtherapy.com) contains pages specifically designed to educate parents about EBP for adolescents with mental health and/or substance use problems. Banners will be placed on the Substance Abuse and Dependence page, along with pages for two conditions that are highly comorbid among ASUDs: Disruptive Behavior Problems and Depression and Related Disorders. Based upon webpage usage statistics at the time of this protocol submission, these three pages respectively received an average of 108, 712, and 354 unique hits per month. Combining these data with national estimates of internet usage [73] and prevalence rates of co-occurring problems among ASUDs [74-76] leads to the conservative estimate that approximately 29–40 webpage visitors per month likely will meet study eligibility criteria. Using another conservative estimate that only 50 percent of visitors will likely participate (due to repeat visitors, ineligibility, and lack of interest), this study will set a recruitment target of four parents per week. Quota sampling will be used to promote equivalence across the online and community-based samples on key demographic (e.g., age, race/ethnicity, socio-economic status, region) and clinical variables (parental substance use, number of concerns about teen substance use endorsed on the screener); if sample differences are detected across the two sampling frames, a propensity weighting approach will be used to balance the samples [77] prior to merging the data.

### Survey analysis

Descriptive statistics will be generated to summarize responses for the market research questions. Additional analyses will be conducted to test the psychometric properties of the new PSQ, including its factor structure, internal consistency, and validity (criterion, convergent, and discriminant). Items with a high proportion of missing data will be eliminated to create a more parsimonious scale. The following analyses are planned: *Factor Structure*. The target sample of 400 and expected questionnaire length of 20 items will enable analyses to be conducted using both Exploratory Factor Analysis (EFA) and Confirmatory Factor Analysis (CFA). EFA will be conducted using principal component analysis as the extraction method and promax as the rotation method. CFA will be conducted to further assess the scale’s structure. Model fit will be evaluated using conventional-fit indices, including RMSEA, CFI, and chi-square [78]. *Reliability*. Internal consistency for each scale will be calculated using Cronbach’s alpha, with values exceeding .7 viewed as evidence of high internal consistency [79]. *Criterion Validity*. Consistent with the initial SERVQUAL validation [39], criterion validity will be tested using global assessments of service expectations on a 10-point scale (1 = poor, 10 = excellent). *Convergent Validity*. Loading of scale items on their corresponding factors will be examined to assess convergent validity. *Discriminant Validity*. Discriminant validity will be tested by constraining each correlation between pairs of factors (one at a time) to unity in the measurement model and repeating the CFA. If the constrained CFA increases chi-square, it will support the distinctiveness of each scale’s component dimensions.

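### Principal components is named as the extraction for the PSQ's exploratory factor analysis, which overstates loadings and makes dimensions look more separate than they are

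*Protocol article*

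**What the plan says.** The section on Phase 2 procedures says: "Phase 2 uses a survey of parents of ASUDs (n = 400) to serve two goals", the first being the psychometric properties of the PSQ. The Survey analysis section says that 400 parents and about 20 items "will enable analyses to be conducted using both Exploratory Factor Analysis (EFA) and Confirmatory Factor Analysis (CFA)". It fixes the exploratory method as follows: "EFA will be conducted using principal component analysis as the extraction method and promax as the rotation method". The next step is: "CFA will be conducted to further assess the scale’s structure". Fit is to be judged by RMSEA, CFI and chi-square. On convergent validity it says: "Loading of scale items on their corresponding factors will be examined to assess convergent validity". It does not say whether these are component loadings or loadings from the confirmatory model. Discriminant validity rests on fixing each factor correlation to 1 in the confirmatory model and looking for a rise in chi-square.

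On the make-up of the sample, the Online recruitment section says that if the clinic and online samples differ, "a propensity weighting approach will be used to balance the samples [77] prior to merging the data". The article does not allocate respondents between the exploratory and confirmatory analyses. It gives no rule for the number of factors and no loading cut-off for keeping an item.

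**The concern.** A component is a weighted sum of the observed items, including their error. A factor in the confirmatory model is a latent variable that explains only what the items share. Naming the first as the extraction for an exploratory factor analysis, and following it with the second, puts two different models in sequence. The gap is large for a scale of this kind, with few items per dimension and possibly modest loadings.

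The effect falls on decisions that Aim 2 depends on. Component loadings are too high, most of all for weak items, so poor items can survive and could be offered as evidence of convergent validity. Component correlations are too low, so overlapping dimensions look separate. The item set and subscales chosen in this way then define the PSQ used for the first hypothesis of the Phase 3 trial.

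A related question is whether the confirmatory analysis has its own respondents. If it does not, the discriminant test is applied to groupings that the same data selected.

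**Working it through.** **Inputs.** From the article: n = 400, 20 items, principal components with promax. Not in the article, so assumed: four factors of five items or five factors of four items; equal true loadings of .4 to .8; factor correlations of .3 or .5. No figure in the plan bears on this point, so there is none to reproduce.

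**Step 1: loadings, by formula.** Take m items per factor, each with true loading l. Items in a block correlate l², so the block's largest eigenvalue is 1 + (m − 1)l². The component loading is

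sqrt[(1 + (m − 1)l²) / m].

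For m = 5, l = .4: sqrt(1.64/5) = .573. For m = 4, l = .4: sqrt(1.48/4) = .608. The formula treats each block alone. The n = 400 columns come from simulated samples of the full 20-item scale with promax.

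| True loading | Formula, m = 5 | Formula, m = 4 | Components, n = 400 | Principal axis, n = 400 |
|---|---|---|---|---|
| .4 | .573 | .608 | .53-.57 | .39-.40 |
| .5 | .632 | .661 | .62-.65 | .49-.50 |
| .6 | .699 | .721 | .69-.72 | .59-.60 |
| .7 | .769 | .786 | .76-.78 | .69-.70 |
| .8 | .844 | .854 | .84-.85 | .79-.80 |

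The overstatement runs from about .04 for strong items to about .17 for weak ones. If, for illustration, items were kept at .50 or more, an average item with a true loading of .4 would pass under components and fail under principal-axis extraction.

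**Step 2: factor correlations.** With true correlation r, the corresponding components correlate

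r × m l² / [1 + (m − 1)l²].

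For m = 5, l = .5: r × 1.25/2, so .3 becomes .19 and .5 becomes .31. In samples of 400 with promax and loadings of .4 to .7, .3 appears as about .11-.25 and .5 as about .16-.40. Principal-axis extraction gives .30 and .49 on the exact population matrices. In samples with loadings near .4 it still falls somewhat short, but less than components do.

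**Step 3: confirmatory fit if the sample is re-used.** This used 150 simulated four-factor populations (loadings .4 to .7, correlation .3, four small cross-loadings, minor misfit). Components with promax assigned and pruned the items, and a maximum-likelihood confirmatory model followed.

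| Confirmatory sample | RMSEA | CFI | CFI at least .95 |
|---|---|---|---|
| Same 400 | .0333 | .951 | 55% |
| Fresh 400 | .0332 | .951 | 56% |
| Other half of a 200/200 split | .0355 | .942 | 41% |

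Re-use gave essentially no optimism in fit when the number of factors was right. The split row reflects the smaller sample.

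**Step 4: discriminant test if the sample is re-used and too many factors are taken.** Here the true scale has one factor, and three components are imposed. The table gives the share of factor pairs declared distinct at a chi-square difference above 3.84. The plan names no cut-off, so 3.84 is an assumption.

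| True loading | Same sample | 200/200 split |
|---|---|---|
| .6 | 93-96% | 6-7% |
| .5 | 95% | 5% |
| .4 | 94% | 8% |

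Whether over-extraction would occur depends on the retention rule and on item strength. Under an assumed eigenvalue-above-1 rule, the one-factor scale yields a second component in about 1% of samples at loadings of .6, and a third in none. At .5 it yields two or more in about 93%. At .4 it yields four or more in practically every sample.

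**The case against.** The strongest objection is that the text never says both analyses use the same parents. Stating that 400 is enough for two analyses fits a planned 200/200 split just as well, and a condensed article may leave that allocation to the full protocol or analysis plan. This stands, so the sample re-use point can only be conditional.

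A reader might go further and infer that the confirmation is circular and that fit, loadings and discriminant tests will all be too favourable. The material does not support that. Fit was not inflated in step 3. Loadings in the confirmatory model are common-factor estimates, which the earlier component step does not inflate. The striking 93-96% in step 4 requires three components to be imposed on a one-factor scale, which the eigenvalue rule would not do at loadings of .6. It becomes a practical risk only with loadings of .5 or below.

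It can also be said that Phase 3 is a randomised comparison of PSQ means, that the mediator analyses are exploratory, and that the study is presented as proof of concept. That is right: extraction choice does not bias the group comparison.

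None of this answers the main point. Components extraction is a stated method, not an omitted detail.

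**Conclusion.** The extraction method is a real and correctable weakness. At n = 400 with 20 items, components turn true loadings of .4, .5 and .6 into about .53-.57, .62-.65 and .69-.72, and shrink factor correlations of .3 and .5 to about .11-.25 and .16-.40. The sizes rest on an assumed four or five equal-sized factors with equal loadings, so they are illustrative. The direction follows from the formulas whenever loadings are below 1. The inflation applies to the component loadings only, and matters to the extent that they decide item retention or are reported as convergent validity.

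The separate-sample point is secondary. The article describes one merged sample and no split, but does not state that respondents are shared. If they are, the exposure lies in the discriminant test when too many factors are drawn from weak items. A claim that the PSQ validation is circular, or that the Phase 3 result is biased, would go beyond the document.

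**What to change.** In the Survey analysis section:

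- Replace principal components with principal-axis or maximum-likelihood extraction, and keep promax.
- State that the loadings used for convergent validity come from the confirmatory (common-factor) model.
- State which respondents each analysis uses. If a split is already planned, one sentence settles this. If the same parents serve both, either label the confirmatory analysis and its discriminant tests as non-independent, or divide the 400 at random into 200 for each step (200/20 = 10 respondents per item, against 400/20 = 20 unsplit).

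The first two changes cost only wording before the data are analysed. The split has a price: confirmatory estimates are less precise, and in step 3 the share of analyses reaching a CFI of .95 fell from 55% to 41%. Labelling the analysis as non-independent avoids that price, but leaves the discriminant test without independent support.

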**Marketing mix elements and key questions.**

Although all four elements of the Marketing Mix are important, scholars in the field of services marketing (the marketing of professional services) have argued that the Product (or Service) component is especially vital, because of the need to understand how customers define a quality service experience. In a widely cited article, Berry, Parasuraman, and Zeithaml (pg. 35) asserted that “service quality has become the great differentiator, the most powerful competitive weapon most service organizations possess,” and they further argue that “it is the customer’s definition of quality, not management that counts” [29]. Services are significantly more difficult to evaluate objectively than products, because they are intangible, heterogeneous over time and across providers, and difficult to reproduce; consequently, customers’ *subjective* perceptions of quality become critically important predictors of whether customers will actually seek out the service [29,30]. Over the past 25 years, the Marketing Science Institute has supported extensive research on customer perceptions of service quality [29-37]. Formative qualitative research in several industry sectors [31,34,38] led to the development of SERVQUAL [39,40] a questionnaire that evaluates perceived service quality (PSQ) across five dimensions: Reliability, Responsiveness, Assurance, Empathy, and Tangibles. The SERVQUAL is widely accepted as the gold-standard measure of PSQ, having been used in over 70 service industries across 17 countries [26,41]. Multiple other measures of PSQ have also been developed and used in marketing research [42,43].

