### Procedures: study phase 3 (Specific Aim 4) — months 43–60

Phase 3 will use a two-group RCT (n = 160) to evaluate the effectiveness of targeted marketing versus standard clinical information in increasing parent impressions of PSQ and persuading parents of ASUDs to seek out information about EBP. Study hypotheses will be tested using the PSQ, which was adapted and validated in Phases 1–2, as well as behavioral indicators of information-seeking. Recruitment will occur using the same eligibility criteria and multimethod, single-mode approach as Phase 2.

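### The Phase 2 discriminant-validity rule accepts any rise in chi-square, which under ordinary maximum likelihood says almost nothing about whether two PSQ dimensions are distinct

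*Protocol article*

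**What the plan says.** The Survey analysis section (protocol article, Phase 2) lists the psychometric checks planned for the new PSQ measure: factor structure, internal consistency, and criterion, convergent and discriminant validity. Discriminant validity is to be tested by "constraining each correlation between pairs of factors (one at a time) to unity in the measurement model and repeating the CFA". The decision rule follows directly: "If the constrained CFA increases chi-square, it will support the distinctiveness" of the dimensions.

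Neither sentence requires the increase to be significant or gives a critical value, degrees of freedom, an alpha level or an allowance for testing several pairs. No other section of the article supplies one. The same section does state a threshold for reliability (Cronbach's alpha above .7). Its statement on fit, "Model fit will be evaluated using conventional-fit indices, including RMSEA, CFI, and chi-square", concerns the overall model and is not a difference test.

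**The concern.** When a model is compared with a restricted version of itself, the restricted version cannot fit better. A rule that looks only at whether chi-square went up therefore gives nearly the same answer whether the two dimensions differ or not. The useful information is in the size of the increase, and the rule does not use it.

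The question is a live one for this instrument. The Qualitative analysis section lists candidate dimensions that plausibly overlap, such as empathy, caring and attentiveness, or access, availability and convenience. The section on the benefits of measuring perceived service quality reports that adaptations of the parent scale have yielded anything from three or four dimensions to six or more. Whether the new PSQ's dimensions are separate is something Phase 2 should be able to answer. The answer is then carried forward: "Study hypotheses will be tested using the PSQ, which was adapted and validated in Phases 1–2".

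**Working it through.** **Stated figure.** The plan attaches no error rate or cut-off to this rule, so there is none to reproduce.

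**Inputs from the article.** "The target sample of 400 and expected questionnaire length of 20 items" (Survey analysis); one correlation fixed at 1 per comparison, so 1 df each. The parent instrument is "a questionnaire that evaluates perceived service quality (PSQ) across five dimensions: Reliability, Responsiveness, Assurance, Empathy, and Tangibles". If five dimensions were kept there would be 5 × 4 / 2 = 10 pairs; the number for the new PSQ is not yet known.

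**Assumed inputs.** Two factors, four items each, multivariate normal data, and equal loadings of .7 (main run) or .6 (second run).

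**Step 1: nesting.** Maximum-likelihood CFA minimises F = ln|Σ| + tr(SΣ⁻¹) − ln|S| − p over the model's parameters, and chi-square = (N − 1) × min F. Fixing the correlation φ at 1 restricts the parameter set. A minimum over a subset cannot be below the minimum over the whole set, so

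Δχ² = χ²(φ = 1) − χ²(φ free) ≥ 0 in every sample.

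Equality requires the free estimate to be exactly 1. With an unbounded estimate that essentially never happens. If the software bounds φ at 1, it happens whenever the estimate reaches the bound.

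**Step 2: simulation, loadings .7, N = 400.** Both models were fitted to each sample; the last two columns use the unbounded fit.

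| True φ | Samples | Any rise, φ unbounded | Any rise, φ bounded at 1 | Δχ² > 3.84 | Δχ² > 7.88 |
|---|---|---|---|---|---|
| 1.00 | 2000 | 100% | 47.5% | 3.8% | 0.5% |
| 0.98 | 500 | 100% | 85.8% | 15.4% | 3.8% |
| 0.95 | 500 | 100% | 99.8% | 66% | 32% |
| 0.90 | 500 | 100% | 100% | 99% | 91.4% |

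With identical dimensions (φ = 1.00) and an unbounded estimate, chi-square rose in 2000 of 2000 samples. The smallest rise was about 9 × 10⁻⁷, the median 0.44 and the mean 0.94. The stated rule thus gives the same verdict at φ = 1.00 as at φ = 0.90. With the bounded estimate, the 3.84 cut-off was exceeded in 2.0% of samples at φ = 1.00.

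**Step 3: second simulation, loadings .6, N = 400, 400 samples with identical dimensions.** Chi-square rose in 99.5% unbounded and 42.5% bounded. The 3.84 cut-off was exceeded in 3% at φ = 1.00, 32% at φ = .95 and 77% at φ = .90. By Step 1 the remaining 0.5% cannot be true decreases; numerical tolerance in the fit is the likely reason, but this was not established.

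**Step 4: several pairs.** For ten pairs at a familywise level of .05, the Bonferroni level is .05 / 10 = .005 per pair, with a 1-df critical value of about 7.88. This is also the first step of a Holm procedure. A fixed cut-off of 3.84 is therefore not compatible with a multiplicity correction; adjusted p-values are the cleaner statement.

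**The case against.** **Shorthand in a condensed article.** Fixing a correlation at 1 and comparing chi-square is the set-up of a difference test. The authors may well have meant a significant increase, and a fuller document may say so. That is a fair account of intent. But the article does not leave the criterion open: it prints a complete if-then rule, and that rule is invalid as printed.

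**The rule can fail.** A reader might infer that the test can never fail and that every pair will be called distinct. The documents do not support that. It holds only for an unbounded correlation under the ordinary maximum-likelihood statistic. With a bound at 1 the difference can be exactly zero. The article names no estimator, and the Online recruitment section allows propensity weighting; with scaled or robust statistics a strict ordering of the two chi-squares is not guaranteed. This narrows the claim but does not rescue the rule, since a false-support rate of 43% to 48% per pair under the bound is still unusable.

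**Phase 3.** A reader might also infer that the randomised comparison rests on an empty test. The Outcomes section plans mean comparisons on the PSQ and names no subscale analysis, and the Survey analysis section attaches no action to the discriminant result. No effect on the trial's sample size, power or mean comparison is shown. This objection stands.

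**Other checks exist.** EFA, overall CFA fit, alpha, loadings and criterion validity are also planned, and Aim 2 covers the PSQ's psychometric properties generally. This also stands: discriminant validity is one component of Aim 2.

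**Conclusion.** The criterion is wrongly stated. At N = 400 it would declare truly identical dimensions distinct in about 100% of samples with an unbounded correlation and in about 43% to 48% with one bounded at 1. An unadjusted 1-df test at .05 would do so in 3% to 4% (2.0% in the bounded run with loadings .7).

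That the direction of change is uninformative follows from nesting and needs no assumption beyond the ordinary maximum-likelihood statistic. The percentages rest on two factors, four items per factor and the assumed loadings. The power of the corrected test depends strongly on the loadings: at a true correlation of .95, the 3.84 cut-off is passed in 32% of samples with loadings of .6 and 66% with .7.

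The consequence is confined to the discriminant-validity claim within Aim 2 and to any interpretation of separate PSQ subscales.

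**What to change.** Replace the decision sentence in the Survey analysis section with:

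*Two dimensions will be considered distinct if fixing their correlation to 1 significantly increases chi-square (1-df chi-square difference test, two-sided familywise alpha .05, Holm-adjusted p-values over all factor pairs). Each factor correlation will be reported with its 95% CI.*

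Add that a non-significant pair will be reported as not shown to be distinct and then reviewed. It should not be merged automatically: non-rejection does not prove identity, and the power figures above show that truly separate but highly correlated dimensions can fail the test. It would also help to state the estimator and whether correlations are bounded at 1.

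The cost is a sentence or two of analysis wording, with no change to data collection or sample size. The small downside is that some dimensions may turn out not to be supported as distinct.
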